## Study assessments

- 1.) All pain scores will be acquired using numeric rating scales from 0 ("no pain") to 100 ("maximum imaginable pain"). Ratings will assess the period of one week before the day of assessment.
- 2.) Pain-related disability, state and trait anxiety, depression and quality of life will be assessed using the following validated questionnaires
  - a.) Pain disability index, PDI [9]
  - b.) State-Trait Anxiety Inventory, STAI [10]
  - c.) Beck Depression Inventory, BDI-II [1]
  - d.) 12-Item Short Form Survey, SF-12 [11]

All ratings will assess the period of one week before the day of assessment.

- 3.) Pain area and widespreadness (Widespread pain index, WPI) will be derived from electronic pain drawings acquired using the tablet PC application "SymptomMapper" developed by our group. Ratings will assess the period of four weeks before the day of assessment.
- 4.) HRV will be measured before and after each floating session using a Nilas MV Diagnostik- und Regulationssystem (Nilas MV GmbH, Hamburg).
- 5.) Unusual bodily sensations during floating will be acquired from electronic drawings with the "SymptomMapper" software.
- 6.) Altered states of consciousness will be assessed using the 5-Dimensional Altered States of Consciousness Rating Scale, 5D-ASC [4].
- 7.) Sleep quality will be assessed with a numeric rating scale. Patients will be asked how much their pain impairs their sleep on a scale from 0 ("not at all") to 100 ("very much").
- 8.) Use of pain medication will be assessed by patients' self report.
- 9.) To assess the treatment belief, subjects will receive the following written question "Which treatment do you believe you received?" and offered the replies "real floating", "placebo floating" or "uncertain".

- 10.) To assess credibility of and expectancy in the treatment, a four-item Borkovec and Nau's self-assessment scale will be used [3].

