## Endpoints

The study has **short-term endpoints** to assess the effect of each single floating session and **long-term endpoints** to assess the effect of a course of five successful floating sessions. While the former will be assessed before and after each floating session, the latter will be assessed one week after the final floating session and in two follow-ups at 12 and 24 weeks after completion. The only exception are pain area and widespreadness that will not be included in the follow-up assessments.

The study is successful, when the primary outcome shows significant differences between the intervention group and the control group at first assessment (one week after the final floating session).

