### Primary outcome (long-term):

The primary endpoint of the study is the reduction of pain (maximum and average) as measured by a numeric rating scale (NRS) retrospectively for one week.

**Secondary long-term outcomes** comprise improvements in

- 1.) Reduction of pain (maximum and average) by 30% or more (dichotomous)
- 2.) Pain-related disability (PDI)
- 3.) Trait Anxiety (STAI Trait)
- 4.) Depression (BDI)
- 5.) Quality of life (SF-12)
- 6.) Quality of sleep (NRS)
- 7.) Use of pain medication

**Secondary short-term outcomes** comprise improvements in

- 1.) Acute pain intensity (NRS)
- 2.) Acute pain area and widespreadness (from electronic pain drawing)
- 3.) State Anxiety (STAI State)
- 4.) Heart rate variability (improvement of sympatho-vagal balance indicated by an increase in HF- and a decrease in LF-HRV)
- 5.) Unusual bodily sensations during floating (electronic drawing)
- 6.) Altered states of consciousness during floating (5D-ASC)

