## Study procedures on each study day

The subject recruitment will start in February 2018 according to the inclusion and exclusion criteria and will be conducted at the Pain Outpatient Department (Schmerzambulanz) of the MHH.

At visit 1 (screening), written informed consent will be obtained. Subjects will undergo a physical examination and medical history taking. In- and exclusion criteria will be checked. Subjects will be familiarized with the floating tank. After this, the primary and secondary long-term outcomes will be assessed, as well as the expectancy/credibility rating.

At visits 2 - 6 (intervention), each separated by  $4 \pm 2$  days, in- and exclusion criteria will be checked again. Secondary short-term outcomes 1, 2 and 3 will be assessed. After this, a 5-minute ECG will be recorded for HRV analysis (short-term outcome 4). Subjects will then put on their bathing suits, take a shower and insert ear plugs before entering the floating tank (Tranquility, Floataway, Hingham, GB). The float itself will take 90 minutes. After the floating session subjects will leave the tank and take a shower to remove excess saline. Another 5-minute ECG will be recorded for HRV analysis (short-term outcome 4), before short-term outcomes 5 and 6 will be assessed.

After the last intervention, the subject is provided with a sealed envelope containing the questionnaires for the assessment of primary and secondary long-term outcomes and discharged.

On day 7 after visit no. 6 the subject is called by telephone and asked to fill out all questionnaires in the envelope and return it by mail.

This will be repeated at 12 weeks and 24 weeks after visit no. 6. Subjects in the intervention and control group will be unblinded after receipt of the last questionnaires.

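### The single one-week recall sentence covers both STAI scales and fits neither the trait outcome nor the before-and-after-session use of the state scale

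*Combined protocol and SAP*

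**What the plan says.** Item 2 of Study assessments puts five constructs under four instruments (PDI, STAI, BDI-II, SF-12): "Pain-related disability, state and trait anxiety, depression and quality of life will be assessed using the following validated questionnaires". It closes with a recall rule that makes no exception: "All ratings will assess the period of one week before the day of assessment".

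The outcome lists in the Endpoints section use the two STAI scales for different purposes. The third secondary long-term outcome is "Trait Anxiety (STAI Trait"; the third secondary short-term outcome is "State Anxiety (STAI State".

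The timing differs accordingly: "While the former will be assessed before and after each floating session, the latter will be assessed one week after the final floating session", with further long-term follow-ups at 12 and 24 weeks. For the long-term outcomes, Study procedures on each study day places the baseline at the screening visit ("After this, the primary and secondary long-term outcomes will be assessed, as well as the expectancy/credibility rating"). The first assessment after treatment follows the last float by a week: "On day 7 after visit no. 6 the subject is called by telephone and asked to fill out all questionnaires in the envelope".

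**The concern.** The protocol separates trait from state anxiety and assigns one to the long-term and the other to the short-term outcomes. That separation is useful only if the two scales capture different things. A common seven-day window removes the distinction.

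For the trait scale, what is at stake is the meaning of the result. If patients answer for the past week only, a change at the first post-treatment assessment describes anxiety in the days since the last float. It would nevertheless be reported under a label that suggests something more lasting.

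For the state scale, what is at stake is whether the outcome can respond at all. A short-term outcome is meant to show what one session does, and a rating that averages over a week has little room to show it.

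**Working it through.** The plan gives no figure to reproduce, and no power or error-rate formula applies. The check compares the recall rule with the outcome lists and the visit schedule.

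**Inputs.** Recall window: 7 days = 7 × 24 = 168 hours (Study assessments, item 2). Float: 90 minutes = 1.5 hours; five sessions at visits 2 to 6, 4 ± 2 days apart; first post-treatment questionnaires on day 7 after visit 6, then at 12 and 24 weeks (Study procedures on each study day). Short-term endpoints before and after each session (Endpoints).

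**1. Is the sentence a rule or a passing remark?** Study assessments sets recall periods item by item: one week for pain scores (item 1), one week for the questionnaires (item 2), four weeks for the pain drawings (item 3). In that setting the item 2 sentence reads as a specification, and both STAI scales are named in the item it closes.

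**2. State scale.** If the two ratings around a session are g hours apart, the shared part of their windows is (168 − g)/168.
- Float alone, g = 1.5: 166.5/168 = 99.1%.
- The documents do not give the full gap, which also includes showers and ECG recordings. With an assumed g of 4 hours: 164/168 = 97.6%.

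Sessions are 2 to 6 days apart, always less than 7. From the second session on, the window therefore also contains at least one earlier float. A seven-day rating cannot isolate the effect of a single session.

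One qualification: the before-and-after timing comes from Endpoints. Study procedures lists short-term outcomes 1 to 3 before the float and names only the ECG and outcomes 5 and 6 after it. Data analysis plans paired t-tests for the short-term outcomes, which is consistent with a before-and-after comparison.

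**3. Trait scale.** Five sessions span four intervals: 4 × 4 = 16 days nominally, with a range of 4 × 2 = 8 to 4 × 6 = 24 days.
- Day 7: the window is the seven days since visit 6, so it covers the time after the last float and none of the preceding course.
- Week 12: 7/84 = 1/12 of the time since visit 6.
- Week 24: 7/168 = 1/24 of that time.

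At each assessment the literal rule yields a rating of the most recent week, while the outcome carries a trait label.

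**4. What cannot be computed.** The documents give no STAI scores and do not reproduce the form's instructions, so the effect of the window on the scores cannot be derived.

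**The case against.** The strongest reply is that the sentence is loose drafting over four instruments and was never meant to alter the STAI. The protocol describes the questionnaires as validated and cites a source for the STAI, which suggests use of the instrument as it stands. The literal reading also gives an implausible result for the state scale. Item 1 has the same looseness: it gives all pain scores a one-week period, although acute pain intensity is a short-term outcome. This reply is fair, and the documents cannot rule it out. It does not remove the need for correction, because Study assessments is where staff and readers learn which period each scale covers, and as written it gives the wrong answer for at least one scale.

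A reader might infer more: that the trait form has been turned into a recent-anxiety form, or that outcome 3 cannot support any conclusion about trait anxiety. The documents do not support that. They do not show the trait form's instructions, do not say they were changed, and do not establish what patients were told.

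Three further points stand and limit the consequence. The rule makes no distinction between groups, so it gives no reason to expect a biased comparison. The 12- and 24-week assessments test whether a change lasts, and calm days just after the last float would not explain a difference there. At day 7, a one-week window also has a plausible purpose, since it keeps the treatment course out of the rating.

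**Conclusion.** The point holds as an internal conflict between Study assessments, item 2, and the outcome definitions in Endpoints. It is clearest for STAI State, where before and after ratings would share roughly 98 to 99% of their window; the lower end rests on the assumed four-hour gap. For STAI Trait it is a mismatch between label and rated period. If the one-week rule was applied, the conclusion should be limited to that period.

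The importance is minor. One of seven secondary long-term outcomes and one of six secondary short-term outcomes are affected, and only in how they can be interpreted or how well they can show a session effect. The primary pain outcome, the success criterion and the sample size do not involve the STAI. The verdict assumes only that the recall sentence means what it says; whether it was followed is unknown.

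**What to change.** In Study assessments, item 2, limit the one-week sentence to PDI, BDI-II and SF-12, provided those three are meant to cover a week. Add that STAI State is rated for the moment of assessment and that STAI Trait is given without a one-week window.

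If data have already been collected, report which instruction patients saw for each STAI scale. If the one-week wording was used for STAI Trait, present outcome 3 as anxiety over the past week and draw no wider conclusion from it.

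The cost is about one sentence, or a changed outcome name in the report. The downside is that a trait score without the window may move less over the study period, so a treatment effect on it may be harder to show.

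### The recall periods set for acute pain, pain drawings and state anxiety contradict their use before and after a single float

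*Combined protocol and SAP*

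**What the plan says.** The Endpoints section introduces the short-term endpoints as a means "to assess the effect of each single floating session" and says that they "will be assessed before and after each floating session". The list that follows has six of them. The first two, pain intensity on the NRS and pain area and widespreadness from the electronic drawing, are labelled acute. The third is STAI State.

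The Study assessments section then sets the rating periods:

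- Item 1 begins "All pain scores will be acquired using numeric rating scales from 0" and, after describing the scale, fixes the period as the week before the assessment day. It makes no exception for acute pain.
- Item 2 covers the questionnaires and names state as well as trait anxiety. It closes with "All ratings will assess the period of one week before the day of assessment".
- Item 3, on pain area and widespreadness, says "Ratings will assess the period of four weeks before the day of assessment".

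No section gives a current-moment instruction for any of the three outcomes. The Study procedures section puts outcomes 1, 2 and 3 before the float. After the float it lists only the second ECG and outcomes 5 and 6. The Data analysis section tests the short-term outcomes with two-tailed paired t-tests.

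**The concern.** A comparison before and after an exposure works only if the second rating can take in the exposure. Here the exposure lasts 90 minutes, while the rating periods are one or four weeks that end before the visit day. If the forms and the tablet follow the Study assessments section, patients are asked about the same past period twice on one day.

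Three of the six short-term outcomes are at stake, including both short-term pain outcomes. A finding of no change could come from the rating period alone. A finding of change could not be attributed to the float unless one knew which period patients had in mind when they answered.

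**Working it through.** The plan states no figure on this point, so there is none to reproduce. The check is a count of days.

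**Inputs.** Recall length w: 7 days for pain scores and STAI State, 28 days for pain area and widespreadness (Study assessments, items 1 to 3). Session length: 90 minutes = 1.5 h (Study procedures). Both ratings are taken around one session (Endpoints), so they fall on the same day D.

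**Literal reading.** A rating on day D that covers the w days before that day runs from D − w to D − 1.

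| Outcome | Rating before float covers | Rating after float covers | Shared days | Day D included? |
|---|---|---|---|---|
| Acute pain NRS | D − 7 to D − 1 | D − 7 to D − 1 | 7/7 = 100% | No |
| STAI State | D − 7 to D − 1 | D − 7 to D − 1 | 7/7 = 100% | No |
| Acute pain area and widespreadness | D − 28 to D − 1 | D − 28 to D − 1 | 28/28 = 100% | No |

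For patients who follow the instruction, the expected paired difference from recalled content is zero, whatever the float does.

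**Lenient reading.** Suppose the period runs up to the moment of rating. The float then makes up 1.5/168 h = 0.9% of one week, or 1.5/672 h = 0.2% of four weeks. These are shares of time and not limits on how far a rating can move. They show only that the lenient reading does not turn the rating into a measure of the session.

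**Can the recall rules be read as applying only to long-term outcomes?** I took the three in turn.

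- Pain NRS: possibly. The primary outcome is a one-week NRS rating, so item 1 may have been written with that in mind.
- STAI State: no. Item 2 names state anxiety, and the outcome lists have it only as short-term. The long-term list has trait anxiety.
- Pain area and widespreadness: not from the outcome lists, which have it only as short-term.

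**Outcomes not affected.** The primary outcome is rated on day 7 after the last float, which suits a one-week recall. Heart rate variability comes from a 5-minute ECG before and after the session. Outcomes 5 and 6 ask about the float itself.

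**Visit schedule.** The Endpoints section requires ratings on both sides of the float, but the Study procedures section lists outcomes 1 to 3 on one side only. As scheduled, the second half of the pair is missing, whatever the recall period.

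**The case against.** The best case for the plan is that current ratings were intended and that the Study assessments section simply fails to say so. The outcome list uses the words acute and state. It attaches a one-week retrospective period to the primary pain rating, and the sample size section does the same for the pain rating used to balance the groups. Those qualifiers would be unnecessary if every pain rating looked back a week. The forms and tablet instructions are not part of the documents, so what patients would be asked is unknown.

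Much of this stands. A reader might infer that the trial is designed to rate acute outcomes over past weeks. The documents do not establish that; they contain two incompatible signals. But the favourable reading does not clear the text, because item 2 names state anxiety, which is only a short-term outcome.

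A second argument concerns the four-week rule. The Endpoints section exempts pain area and widespreadness from the 12- and 24-week follow-ups, as though they otherwise belonged with the long-term measures. The rule may therefore have been meant for a baseline or one-week drawing. That is possible, but no such drawing appears among the long-term outcomes, so the ambiguity remains for the plan to resolve.

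A reader might also infer that any change seen under the recall wording would be a demand effect. That does not follow. A patient who reports current pain despite the instruction may be reporting real relief, or present relief may colour the recall. Nor does the overlap between the recall periods of successive visits matter here, because the comparison is within a session.

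**Conclusion.** The Study assessments section contradicts the Endpoints section and its outcome list for short-term outcomes 1 to 3. Followed literally, the ratings before and after a float share 100% of their recall period and exclude the session. The paired difference then cannot show the effect of the float, and any result, null or not, would be uninterpretable. The visit schedule adds a second conflict by omitting the rating after the float.

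This rests on three assumptions: both ratings fall on the visit day, the paired t-test compares before with after, and the instructions given to patients match the written rule. The first two follow from the Endpoints section. The third cannot be checked from the documents.

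This should be fixed, but it does not threaten the trial's main conclusion. A reader might take it to undermine the pain results as a whole. It does not: the success criterion, the sample size and the primary outcome do not depend on these ratings.

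**What to change.** 1. In Study assessments, limit the one-week recall to the long-term outcomes. State that the acute pain NRS, the pain drawing at visits 2 to 6 and STAI State are rated for the current moment, not over one or four weeks. If a four-week drawing is wanted at some other visit, name the visit and list it as a separate measure.
2. In Study procedures, list outcomes 1 to 3 after the float as well as before it, as the Endpoints section requires.
3. If data have already been collected, report the wording that patients actually saw for each of the three outcomes. The supplement's opening page says that the protocol was not altered after ethics approval, so no later version settles the matter.

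The cost is new instruction text on the NRS, the tablet drawing and the state anxiety form. The visit schedule gains short ratings after each float, which the Endpoints section already calls for. The drawback is that session drawings will not be comparable with any four-week drawing.

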## Study population / Sample size calculation

Sample size calculation is based on a previous explorative studie [5] that showed significant differences between a treatment and a no-treatment group:

|             | Treatment (20) | No-treatment (17) |
|-------------|----------------|-------------------|
| Pain before | 61.75 ± 18.78  | 59.06 ± 17.68     |
| Pain after  | 37.25 ± 30.22  | 60.41 ± 17.21     |

With this number we compute the difference post-pre, which yields  $-24.50 \pm 35.58$  for the treatment group and  $1.35 \pm 24.67$  for the no-treatment group. These differences give a Cohen's d-value of 0.83.

For a two-tailed, two-sample t-test, it means that we need a sample size of 24 subjects per group ( $\alpha=0.05$ ,  $1-\beta=0.95$ , allocation ratio 1:1). To account for attrition we will recruit 25 patients per group, i.e. 75 in total. Drop-outs will be replaced should the size of any group drop below 24 patients.

Groups will be balanced for age, gender and average pain intensity (retrospective NRS rating of the last week), and subjects will be recruited according to the following criteria.

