## Rationale and Objectives

In recent years there has been a novel approach for the treatment of chronic pain: Floatation REST (restricted environmental stimulation therapy). Floating is a therapeutic approach developed in the 1950s [6, 7] which patients float in a specialized pool or tank on water that contains high concentrations of Epsom salt (Magnesium sulfate). Water is kept at skin temperature (35-36°C) and the pool or tank is shielded to provide almost complete darkness and silence. This therapeutic approach has proven to be effective in alleviating chronic pain [2].

While the high salinity of the water allows effortless floating and thus leads to muscle relaxation, the dark and silent environment without somatosensory stimulation greatly reduces sensory input. Thus, the two main mechanisms through which floatation REST may influence pain are the floatation itself and the sensory deprivation.

Due to the difficulties associated with designing a credible placebo control there have been no randomized controlled trials (RCTs) with patients blinding so far. Such blinding, however, is crucial, as the futuristic design of the pools / tanks and the unusual form of intervention are prone to elicit large placebo effects.

Here, we plan to conduct the first patient blinded RCT with a credible placebo control for floating and a no-treatment group.

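### The stated 95% power comes from floating versus no treatment, not from the placebo comparison that decides the trial; even for no treatment, 24 per group gives 80%

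*Combined protocol and SAP*

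**What the plan says.** The section Study population / Sample size calculation relies on one exploratory study that "showed significant differences between a treatment and a no-treatment group". It tabulates pain before and after for 20 treated and 17 untreated patients and turns these into changes of -24.50 ± 35.58 and 1.35 ± 24.67. It then says "These differences give a Cohen's d-value of 0.83" and concludes: "For a two-tailed, two-sample t-test, it means that we need a sample size of 24 subjects per group", with alpha 0.05, power 0.95 and "allocation ratio 1:1". For attrition it adds one patient per group: "To account for attrition we will recruit 25 patients per group, i.e. 75 in total".

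The section Endpoints sets the criterion: "The study is successful, when the primary outcome shows significant differences between the intervention group and the control group at first assessment". Data analysis repeats it as p < 0.05 between those two groups. Study Design defines the control group as a placebo form of floating with low buoyancy and added sensory stimuli. The waiting-list group is a third arm and has no part in the success criterion. Rationale and Objectives says of floating that the look of the equipment and "the unusual form of intervention are prone to elicit large placebo effects".

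**The concern.** The effect used for sizing and the effect being tested come from different contrasts. The first contains everything that separates floating from doing nothing, including any placebo response. The second contains only what full floating adds to placebo floating. The two are equal only if placebo floating does no better than the waiting list, which sits badly with the plan's own reason for having a placebo arm.

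The power figure is doubtful for a second, separate reason: 24 per group looks too few for 95% power at d = 0.83, whichever contrast is meant.

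At stake is what the protocol tells its readers. They would take 95% as the chance of detecting a specific effect of floating in what is presented as the first patient-blinded randomised trial of it. The plan nowhere says which difference from placebo floating the trial can detect.

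**Working it through.** **1. The plan's effect size.** The inputs are the before and after means and SDs in the sample size section.

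- Change SD, treatment: √(18.78² + 30.22²) = 35.58.
- Change SD, no treatment: √(17.68² + 17.21²) = 24.67.
- Difference in change: 1.35 − (−24.50) = 25.85 points.
- Pooled SD: √[(19 × 35.58² + 16 × 24.67²)/35] = 31.07.
- d = 25.85/31.07 = 0.83.

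The effect size reproduces. The change SDs match the plan exactly when the term −2·r·SDpre·SDpost is left out, so the plan has implicitly set the pre-post correlation r to zero.

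**2. The plan's sample size.** Two-sided two-sample t-test (noncentral t), alpha 0.05, 1:1, d = 0.83:

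- Power 0.95 needs 39 per group (38 by normal approximation).
- Power 0.90 needs 32 per group.
- Power 0.80 needs 24 per group.
- One-sided testing at power 0.95 would still need 33 per group.
- 24 per group gives 80% power; the 25 to be recruited give 82%.

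Of these variants, only power 0.80 with the two-sided t-test the plan names returns 24. The stated 0.95 does not follow from the plan's own d.

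**3. The primary contrast.** The documents give no effect of floating against placebo floating, so a range has to be shown. Two quantities are assumed:

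- f, the share of the 25.85 points that placebo floating reproduces;
- r, the pre-post correlation, applied to both groups.

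The pooled SD is taken to be the same as in the planning data. Then

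- SD of change in each group = √(SDpre² + SDpost² − 2·r·SDpre·SDpost), pooled with weights 19 and 16;
- d = 25.85 × (1 − f)/pooled SD.

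For example, at r = 0 and f = 50%, d = 12.93/31.07 = 0.42.

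With 24 per group the smallest d detectable with 80% power is 0.826. Multiplied by the pooled SD, this gives the detectable difference in points.

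| r (assumed) | Pooled SD | Detectable at 80% power | Power, f = 0% | f = 25% | f = 50% | f = 75% |
|---|---|---|---|---|---|---|
| 0 | 31.07 | 25.7 | 80% | 56% | 29% | 11% |
| 0.3 | 26.40 | 21.8 | 91% | 70% | 38% | 13% |
| 0.5 | 22.77 | 18.8 | 97% | 82% | 49% | 16% |
| 0.7 | 18.42 | 15.2 | 99.7% | 95% | 66% | 22% |

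At r = 0 the difference needed from placebo floating, 25.7 points, is practically the whole floating-versus-nothing effect of 25.85.

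**The case against.** The best defence concerns size. Zero correlation is conservative if repeated pain ratings in the same patient are positively correlated, and the true change SD would then be smaller than 31.07. At r = 0.5 with a 25% placebo share, power is still 82%; at r = 0.7 it is 95%. This stands, and it rules out quoting the r = 0 row alone. It does not rescue the stated figure: the plan gives no correlation, does not argue from one, and computes with d = 0.83. At a 50% share, power is no higher than 66% anywhere in the table.

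A second defence is that the plan openly names the source of its effect and notes that no patient-blinded randomised trial existed. Using no-treatment data is therefore understandable. That explains the choice but does not make the resulting power a property of the placebo comparison.

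A reader might go further and infer that the trial can detect only a very large specific effect, or that a null result will be taken to show floating equals placebo. The documents support neither. The first depends on an unknown correlation. As to the second, Endpoints and Data analysis define only when the study is positive and make no equivalence claim. Nor do the documents say how large the placebo response will be; they call floating prone to it and give no figure.

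**Conclusion.** The point holds in two parts.

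- **Comparator.** The power statement describes floating versus no treatment. The deciding test is floating versus placebo floating, for which the plan has no target difference and no argument for carrying the effect over. This rests on the text alone and needs no assumption.
- **Arithmetic.** On the plan's own inputs, 24 per group gives 80% power, not 95%; 95% needs 39 per group. This applies even to the no-treatment contrast.

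The size of the shortfall for the primary test is uncertain. For placebo shares of 25% to 75% and correlations of 0 to 0.7, power with 24 per group runs from 95% down to 11%. It is tempting to conclude that the trial is underpowered and must be enlarged. That is not established: a small placebo response with a moderate or high correlation would leave adequate power. What is established is that the protocol claims a power it has not shown for its primary test.

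**What to change.** Edit the section Study population / Sample size calculation:

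1. Replace the stated power of 0.95 with 0.80, and say that it refers to intervention versus no treatment with zero pre-post correlation. Labelling the contrast without changing the number would leave a wrong figure in place.
2. For the primary contrast, intervention versus placebo floating, state the difference that 24 per group can detect with 80% power: d = 0.83, or about 26 NRS points at r = 0, 19 at r = 0.5 and 15 at r = 0.7. Beside it give the power for placebo shares of 25%, 50% and 75%: 56%, 29%, 11% at r = 0; 82%, 49%, 16% at r = 0.5; 95%, 66%, 22% at r = 0.7. Mark shares and correlations as assumed.

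The cost is protocol wording and a less favourable stated power. The edit adds no patients and leaves the primary test as it is.
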